### Secondary outcome measures

#### Cognitive assessments

A comprehensive neuropsychological test battery, based on the Sydney Memory and Ageing Study (detailed in Brodaty et al. [2]), measuring the five cognitive domains of memory, executive function, attention/processing speed, language, and visuospatial abilities and allowing for comparison with normative demographic-adjusted data was selected. The compendium of tests is detailed in Table 2.

#### Mood and quality of life

The 21-item Depression, Anxiety, Stress Scale (DASS-21) and the Quality of Life in Alzheimer’s Disease (QOL-AD) scale will be used to assess mood and quality of life, respectively.

#### Physiological assessments

Mechanisms of action of SLT will be assessed using central and autonomic nervous system measures of EEG, electrocardiogram (ECG), skin conductance, peripheral pulse pressure, and brain blood flow (common carotid artery ultrasound) at rest and in response to audio/visual stimuli to index changes in psychophysiological processes.

#### Inflammatory markers

Blood samples will be collected from all participants to further assess the mechanisms of action of SLT via change in serum inflammatory marker concentrations, including homocysteine [59], α1-antichymotrypsin [60, 61], interleukin-6 (IL-6) [60], IL-1β [62], and tumour necrosis factor alpha (TNF-α) [62]. DNA will also be extracted from the blood samples, and genetic variants identified in genome-wide association studies will be investigated due to their association with Alzheimer’s disease risk; subgroup analyses (e.g. APOE-E4 carriers/non-carriers) will also be conducted.

### Randomisation and allocation concealment

A university staff member, external to the research team, conducted computerised random sequence allocation using a unique random number generator in Microsoft Excel. A permuted block randomisation strategy was used with an allocation ratio of 1:1. Allocation was concealed using batch numbers generated with the unique random number generator by the same staff member; these were sent directly to the manufacturer. After eligibility is confirmed, participants are allocated to the next numbered box of product by a member of the research team. This is a double-blind trial, so both participants and the research team are blinded to allocation. Furthermore, all data analyses will be conducted blinded to treatment allocation.

### Statistical analyses and data management

The study will largely employ a mixed-model design with a between-subjects factor of group (treatment vs. placebo) and within-subjects factor of time (baseline vs. endpoint). Analyses of variance (ANOVAs) will be conducted to assess differences in continuous outcome measures between the two groups. All tests will be one tailed, α = 0.05. As there are only two testing points for the primary outcome measures (baseline and endpoint), data from any participants failing to complete follow-up will not be included in the final analysis.

All data will be stored on a secure server with two back-up copies on external hard drives. Paper-based forms will be digitised and the original copies stored in locked filing cabinets in secure rooms that require swipe card access at Western Sydney University Campbelltown campus. All participants are de-identified upon randomisation and referred to on all forms with a participant ID. A password-protected spreadsheet stored on the secure server links participant names to ID codes to all for re-identification to occur if required. As this is a relatively small investigator-initiated pilot trial, a data monitoring committee and auditing process are not required.

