**Discussion:**

This study is a 12-week, randomised, double-blind, placebo-controlled trial. Primary and secondary outcome measures will be compared between treatment and placebo groups at baseline and endpoint. Data from this pilot study will inform a larger, more highly powered clinical trial if the findings are positive.

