### Sample size

There are no similar studies using SLT for the proposed study duration (12 weeks) in an MCI cohort. Thus, we selected a well-designed study that used the same primary outcome measure and a similar cohort with a 16-week intervention. That study also provided effect sizes at midpoint (8 weeks) [53]. Craft et al. [53] demonstrated significantly improved delayed recall scores on the Logical Memory Story A subtest of the Wechsler Memory Scale, 4th Edition (WMS-IV) following 8 weeks of 20 IU insulin: a treatment group × time interaction, *p* = 0.020, Cohen’s *f* = 0.36.

We utilised this effect size to conduct an a priori sample size calculation based on the Logical Memory Story A subtest of the WMS-IV. To detect an effect size of Cohen’s *f* = 0.36 at α = 0.05 and 80% power, 63 participants across two groups are required. Allowing for a 20% dropout, this means that 76 participants (38 per group) are required; we rounded this to 80 participants to facilitate a permuted block randomisation strategy. Note also that because this study is a pilot efficacy study (phase II), a larger sample size to reach a higher degree of statistical power is not required.

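### The planned group × time ANOVA is in effect a change-score test; using the baseline as a covariate (ANCOVA) would be more precise at almost no cost

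*Protocol article*

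**What the plan says.** The section on statistical analyses and data management in the protocol article describes a "mixed-model design with a between-subjects factor of group (treatment vs. placebo) and within-subjects factor of time (baseline vs. endpoint"). It adds: "Analyses of variance (ANOVAs) will be conducted to assess differences in continuous outcome measures between the two groups". For the primary outcomes the visits are limited: "As there are only two testing points for the primary outcome measures (baseline and endpoint"), and "data from any participants failing to complete follow-up will not be included in the final analysis". The same section sets the test level: "All tests will be one tailed, α = 0.05". Baseline enters only as a level of the time factor, never as a covariate.

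The sample size section takes its effect from an earlier insulin study, observed "following 8 weeks of 20 IU insulin: a treatment group × time interaction", with Cohen's f = 0.36. It concludes: "0.36 at α = 0.05 and 80% power, 63 participants across two groups are required". A 20% dropout allowance gives 76, rounded up to 80.

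**The concern.** With one baseline and one endpoint value per participant, the group × time interaction compares mean change between arms. A change score subtracts the whole baseline value. When the regression slope of endpoint on baseline is below 1 (with equal SDs, when r is below 1), that removes more than the baseline predicts and adds noise. ANCOVA estimates the slope and removes only the predictable part. Under randomisation both methods target the same treatment effect, so the difference is one of precision.

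Precision matters here. The article's discussion lists 80% power as the trial's first limitation, participants without follow-up are dropped, and the results are meant to inform a larger trial. The baseline values needed for the adjustment are already collected.

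**Working it through.** **Inputs from the protocol article.** f = 0.36, α = 0.05, 80% power, 63 evaluable participants, 20% dropout, 80 recruited (sample size section); two time points, completers only, one-tailed tests (statistical analyses section); 1:1 allocation (randomisation section). 80 × 0.8 = 64 completers, or 32 per arm.

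**Assumptions, not in the article.** Equal SDs at baseline and endpoint; a baseline–endpoint correlation r, shown over a range; f = 0.36 read as the two-group effect on the change-score scale, so d = 2f = 0.72. The article reports no correlation, SD or variance of change for any primary outcome.

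**Step 1: reproduce the plan's figure.** Noncentral F with 1 and N − 2 degrees of freedom and λ = N·f². At two-sided 0.05, N = 62 gives power 0.796 and N = 63 gives 0.803. The stated 63 reproduces. At N = 64 the power is 0.809. A one-sided test at 0.05 would need about 50, so 63 is a two-sided figure. For that reason both sidednesses are shown below.

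**Step 2: the interaction is the change-score test.** In one simulated data set (32 per arm, r = 0.7) the group × time F and the squared t on change were both 8.3669, as the algebra requires.

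**Step 3: compare variances.** Per participant, with common SD s:

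- Var(change) = 2s²(1 − r)
- Var(endpoint given baseline) = s²(1 − r²)
- Ratio = (1 − r²) / [2(1 − r)] = (1 + r)/2, so the reduction is (1 − r)/2

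Simulation at 32 per arm (6,000 runs per r) gave reductions of 23%, 20%, 14% and 8% at r = 0.5, 0.6, 0.7 and 0.8. These are mostly a little below the formula (25%, 20%, 15%, 10%) because the slope is estimated. The mean estimate was about 0.50 by both methods for a true effect of 0.5, so neither is biased.

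**Step 4: turn this into power and numbers.** The effective d under ANCOVA is 0.72/√((1 + r)/2), with 61 error degrees of freedom at N = 64. Completers needed for the precision that the change score has at 64 are 64(1 + r)/2.

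| Analysis | Variance reduction | Power, two-sided 0.05 | Power, one-tailed 0.05 | Completers for equal precision |
|---|---|---|---|---|
| Change score (as planned) | – | 81% | 89% | 64 |
| ANCOVA, r = 0.5 | 25% | 91% | 95% | 48.0 |
| ANCOVA, r = 0.6 | 20% | 89% | 94% | 51.2 |
| ANCOVA, r = 0.7 | 15% | 87% | 93% | 54.4 |
| ANCOVA, r = 0.8 | 10% | 85% | 91% | 57.6 |

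The saving runs from 64 − 57.6 = 6.4 to 64 − 48 = 16 completers. Outside this range, the variance reduction is 35% at r = 0.3 and 5% at r = 0.9; at r = 0.9 two-sided power is 83%.

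**The case against.** The strongest reply is that nothing here is an error. The planned test is valid and unbiased, the 63 reproduces, and a condensed article may leave covariates to an analysis plan that is not shown. The size of the gain is also unknown because the article gives no r. Under the planned one-tailed test, power for the interaction is already 89%, so the gain is about 3 to 6 percentage points for r = 0.8 to 0.5, and about 1 point at r = 0.9.

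Most of that stands and limits the point to efficiency. It does not remove it: the article does name a model, that model uses the baseline as a repeated outcome, and with equal SDs ANCOVA has the smaller large-sample variance at every r below 1.

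Two stronger readings are tempting, and the article supports neither.

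- A reader might infer from the wording about differences between the two groups that the group main effect is the treatment test. That effect averages baseline with endpoint and would estimate only half the benefit. But the trial is sized on a group × time interaction and the design defines both factors, so the interaction is the implied test.
- A reader might infer from the abstract's discussion, "Primary and secondary outcome measures will be compared between treatment and placebo groups at baseline and endpoint", that significance tests at baseline are planned. It is a loose summary of the group and time factors, and the analysis section plans no separate baseline test.

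**Conclusion.** The point holds as a nearly free gain in precision, not as a fault that invalidates the trial or its sample size. The direction of the gain needs only equal SDs and r below 1, in large samples. Its size is conditional: the 10% to 25% range applies only if r is between 0.8 and 0.5, and the power figures also need f = 0.36 to be on the interaction scale. If r is near 0.9, the benefit is small.

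**What to change.** In the statistical analyses section, state that each continuous outcome will be analysed by ANCOVA, with the endpoint value as response, group as the factor of interest and that outcome's own baseline value as covariate. Report the adjusted mean difference with its 95% CI as the treatment effect. This also gives one signed coefficient as the explicit treatment effect.

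The cost is a sentence in the plan and one error degree of freedom (62 to 61 with 64 completers). Visits, measurements and recruitment stay as they are. The sample size need not change.

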### Compliance, success of blinding, safety, and adverse events

After baseline measurements, the first 6 weeks of medication will be dispensed. The second 6 weeks of medication will be dispensed at the midpoint of the study. An additional week of medication (7 weeks total) will be provided at both baseline and midpoint in case there is an unforeseen delay in attending the follow-up appointments. Participants will be required to return any unused medication at midpoint and endpoint; this will be used to determine compliance. The number of returned capsules will be counted by a university staff member external to the research team to further reduce the potential of unblinding. The blood samples collected at baseline, midpoint, and endpoint will also be used in a separate pharmacokinetics study to assess the plasma concentrations of bioactive components of SLT. Eight SLT markers will be assessed: ginsenosides Rg1, Re, Rb1, and Rc and ginkgolides A, B, C, and bilobalide.

At the study midpoint and endpoint, participants will be asked to which treatment condition they think that they have been allocated. Responses of SLT, placebo, or unknown will be recorded. Responses will be checked against the condition allocated at the end of the trial to assess success of blinding. An exit interview will be conducted upon study completion to ascertain further information about participants’ experiences during the trial, e.g. information on health-related expectations, factors influencing compliance/adherence, and any impacts that the trial medication might have had on quality of life. Participants who exit the study early will be contacted via telephone and requested to complete the exit interview.

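### Having only two testing points does not justify a completers-only change analysis as the sole analysis; it can bias the SLT-placebo comparison in either direction

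*Protocol article*

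**What the plan says.** Under Statistical analyses and data management, the protocol article plans a group (SLT or placebo) by time (baseline or endpoint) ANOVA. It then states that "data from any participants failing to complete follow-up will not be included in the final analysis". The only reason offered is that the primary outcomes have just these two assessments. The same paragraph adds: "All tests will be one tailed, α = 0.05".

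Under Sample size: "Allowing for a 20% dropout, this means that 76 participants (38 per group) are required". The target was then raised: "we rounded this to 80 participants to facilitate a permuted block randomisation strategy".

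Under Compliance, success of blinding, safety, and adverse events: "Participants who exit the study early will be contacted via telephone and requested to complete the exit interview". Capsule counts are also taken at midpoint and endpoint.

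**The concern.** The sentence fixes both the analysis set and the treatment of missing endpoints, so this is not a matter left open for a statistical analysis plan. A plan that kept everyone as randomised would contradict it.

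The stated reason does not carry the rule. A single follow-up limits what can be recovered about a leaver, but it does not force exclusion. The baseline score is known, and adherence and exit information may be too. Nor does it justify making the completers' change score the only analysis. With two time points, the group-by-time test is a test of the difference in mean change. Change depends on baseline, so this comparison can be wrong even when loss depends on nothing but the baseline score.

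The primary aim is efficacy on cognition, and positive findings are to lead to a larger trial. A selection effect among leavers would therefore feed directly into that decision.

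**Working it through.** **The plan's own figures.** For two equal groups, f = 0.36 corresponds to d = 2 × 0.36 = 0.72. With a noncentral F test (1 and N − 2 df, noncentrality N × 0.36²) at α = 0.05:
- N = 62 gives power 0.796 and N = 63 gives 0.803, so the stated 63 reproduces.
- 63 × 1.2 = 75.6, the stated 76. Dividing instead, 63 / 0.8 = 78.75, or 79. The planned 80 covers both.
- 80 × 0.8 = 64 analysed and 16 left out. Power at 64 is 0.809.

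The sample size thus absorbs the loss. What remains is selection.

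**General formula.** Let p be the share lost in an arm and d the leavers' mean change minus the stayers' mean change, in SD of the score. The completers' SLT − placebo difference is then biased by −(p_SLT × d_SLT − p_plc × d_plc). With 20% loss per arm:
- d equal in both arms: bias 0.
- SLT leavers 0.5 SD worse, placebo leavers no different: −(0.2 × −0.5) = +0.10.
- Placebo leavers 0.5 SD worse, SLT leavers no different: −0.10.

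With 30% SLT and 10% placebo loss, and leavers 0.5 SD worse in both arms: −(0.3 × −0.5 − 0.1 × −0.5) = +0.10.

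**Case A: loss depends only on baseline.** Assumptions, none from the document: baseline-endpoint correlation 0.7; no true effect; SLT loss of 40% in the lowest 40% of baseline scores and 6.7% above (0.4 × 0.4 + 0.6 × 0.067 = 0.20); placebo loss of 20% at random.
- Mean baseline is −0.966 SD in the lowest 40% and +0.644 SD in the rest.
- SLT completers' mean baseline: (0.24 × −0.966 + 0.56 × 0.644) / 0.80 = +0.161 SD.
- Expected change: (0.7 − 1) × 0.161 = −0.048 SD. Placebo completers: 0.

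The change comparison is off by about −0.05 SD, against SLT. If high scorers left instead, the sign would reverse. A simulation gives the same value, and a baseline-adjusted analysis of the completers alone gives 0.00.

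**Case B: SLT leavers do worse for reasons not recorded.** Assumptions: 20% loss per arm (32 completers each), no true effect, SLT leavers 0.25, 0.5 or 1.0 SD worse than SLT stayers, leaving unrelated to baseline, placebo leavers no different. The bias is 0.2 times the difference. SD of change is √(2(1 − correlation)): 0.775 at 0.7 and 1.0 at 0.5. The standard error is SD × √(2/32) = SD × 0.25. One-tailed rejection at 0.05 comes from a noncentral t with 62 df and noncentrality bias / (SD × 0.25).

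| SLT leavers worse by | Bias towards SLT | Error, SD of change 1.0 | Error, SD of change 0.775 |
|---|---|---|---|
| 0.25 SD | 0.05 SD | 7.4% | 8.2% |
| 0.5 SD | 0.10 SD | 10.6% | 12.8% |
| 1.0 SD | 0.20 SD | 19.7% | 26.7% |

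With an SD of change of 1.0, 0.10 to 0.20 SD is 14% to 28% of the planned 0.72 (0.10 / 0.72 and 0.20 / 0.72).

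**What imputation does in Case B.** Leavers' baselines resemble stayers' baselines, so imputing from baseline within arm gives leavers the stayers' expected endpoint. The imputed arm mean equals the completer mean, and the bias stays at +0.05, +0.10 or +0.20 SD.

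**The case against.** The strongest reply is that including leavers recovers little. With one follow-up and only endpoints missing, their baselines add almost nothing to the treatment contrast once baseline is adjusted for. In Case A, adjustment works on completers alone; in Case B, baseline-based imputation changes nothing. Both statements are right. The fault in Case A is the unadjusted change analysis combined with selective loss, and only a sensitivity analysis that varies the leavers' outcomes addresses Case B. Better imputation needs data that predict the missing endpoint. The document does not establish that these exist: the midpoint visit is 30 minutes and its content is in a figure not shown.

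It can also be said that this is a declared phase II pilot, that the exclusion is stated openly and that the sample size allows for it. This lowers the severity but does not supply a reason for the rule.

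Three stronger readings are tempting and not supported:
- That the rule does bias the trial towards SLT. The direction depends on who leaves, and the bias can be zero or against SLT. The 20% is a planning allowance, not an observed or forecast rate.
- That people who stop capsules are excluded. The sentence removes those without follow-up; someone off treatment who attends the endpoint visit stays in. The telephone exit interview does not show that such visits are refused.
- That an as-randomised statement or sensitivity analysis is missing. A condensed article may leave these to fuller documents. The point rests on the exclusion sentence alone.

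**Conclusion.** The point holds in a limited form. The completers-only rule is stated outright, and its sole reason, two testing points, does not justify it as the only analysis. It leaves the primary comparison dependent on an untested assumption about roughly 16 of 80 participants. The plausible error runs from none, through about 0.05 SD against SLT (Case A), to 0.05 to 0.20 SD in favour of SLT (Case B, with one-tailed error of about 7-8% to 20-27%). Every one of these sizes rests on assumed correlations and leaver-stayer differences that the document does not give. Power is not the issue. Severity: should be fixed, not a fatal flaw.

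**What to change.** Replace the exclusion sentence so that:
1. The primary analysis includes all randomised participants as allocated and adjusts for baseline. This can be a baseline-constrained longitudinal model, or ANCOVA with multiple imputation by arm using baseline cognition and any adherence, midpoint or exit data that prove predictive.
2. A delta-adjusted (missing-not-at-random) sensitivity analysis shifts the leavers' outcomes separately by arm and reports how large a shift would change the conclusion. This is the part that addresses Case B.
3. The completer analysis is kept as supportive.

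As a safeguard, say that participants who stop capsules are still invited to the endpoint visits. These visits and their travel reimbursement are already planned for each participant.

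Cost: revised wording, modest extra analysis, and possibly a slightly less favourable or less precise estimate. No sample size figure changes.

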### Compliance, success of blinding, safety, and adverse events

After baseline measurements, the first 6 weeks of medication will be dispensed. The second 6 weeks of medication will be dispensed at the midpoint of the study. An additional week of medication (7 weeks total) will be provided at both baseline and midpoint in case there is an unforeseen delay in attending the follow-up appointments. Participants will be required to return any unused medication at midpoint and endpoint; this will be used to determine compliance. The number of returned capsules will be counted by a university staff member external to the research team to further reduce the potential of unblinding. The blood samples collected at baseline, midpoint, and endpoint will also be used in a separate pharmacokinetics study to assess the plasma concentrations of bioactive components of SLT. Eight SLT markers will be assessed: ginsenosides Rg1, Re, Rb1, and Rc and ginkgolides A, B, C, and bilobalide.

At the study midpoint and endpoint, participants will be asked to which treatment condition they think that they have been allocated. Responses of SLT, placebo, or unknown will be recorded. Responses will be checked against the condition allocated at the end of the trial to assess success of blinding. An exit interview will be conducted upon study completion to ascertain further information about participants’ experiences during the trial, e.g. information on health-related expectations, factors influencing compliance/adherence, and any impacts that the trial medication might have had on quality of life. Participants who exit the study early will be contacted via telephone and requested to complete the exit interview.

To monitor safety, participants will be referred to a local commercial laboratory (Laverty) at screening and endpoint. Standard blood safety tests (full blood count and liver and renal function tests) will be carried out. If participants receive an abnormal blood safety test result at baseline, they will not be enrolled in the study, and they will be encouraged to follow up their results with their regular health professional. Adverse events will be closely monitored throughout the course of the study. In the case of a serious adverse event, if the study drug is suspected as a potential cause and identifying treatment allocation is essential to the participant receiving appropriate medical care, unblinding of that participant only will occur. This will be done by the university staff member external to the research team who generated the computerised random sequence allocation.

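### The only follow-up described for early leavers is a telephone exit interview, and the analysis drops them, so about 16 of 80 may lack a week-12 outcome: a selection-bias risk, not a loss of planned power

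*Protocol article*

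**What the plan says.** The section Compliance, success of blinding, safety, and adverse events names one step for people who leave: "Participants who exit the study early will be contacted via telephone and requested to complete the exit interview". The interview topics are offered as examples: "information on health-related expectations, factors influencing compliance/adherence, and any impacts that the trial medication might have had on quality of life". No cognitive test, capsule count or treatment guess is among them.

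The same section ties the other two measures to visits: "Participants will be required to return any unused medication at midpoint and endpoint; this will be used to determine compliance", and "At the study midpoint and endpoint, participants will be asked to which treatment condition they think that they have been allocated". The midpoint is at week 6, when the second supply is dispensed.

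Statistical analyses and data management gives its reason, "As there are only two testing points for the primary outcome measures (baseline and endpoint"), and draws the consequence that "data from any participants failing to complete follow-up will not be included in the final analysis".

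Sample size takes a Cohen's *f* of "0.36 at α = 0.05 and 80% power, 63 participants across two groups are required". It continues: "Allowing for a 20% dropout, this means that 76 participants (38 per group) are required". That number is then rounded up to 80.

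Neither the exit-interview sentence nor the exclusion sentence separates stopping capsules from leaving the study.

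**The concern.** Taken together, these sentences describe an early-exit procedure that does not seek the primary outcome and an analysis that removes whoever lacks it. The co-primary tests are given only at baseline and week 12, so an early leaver has no later cognitive score. A statistical analysis plan can change the analysis set or impute, but it cannot recover a test that nobody asked for. The decision therefore belongs in the protocol.

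At stake is the comparability of the arms. Exclusion depends on something that happens after randomisation and may be related to treatment, such as intolerance or a sense of no benefit. If the leavers differ from the stayers, and differ by another amount in the other arm, the completers' contrast no longer estimates the effect in everyone randomised. The trial's primary aim is efficacy, and its result is meant to inform a larger study.

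A smaller issue concerns exposure and blinding. Those who leave before the midpoint have no scheduled capsule count or treatment guess, although the trial intends to telephone them anyway.

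**Working it through.** **Inputs.** From Sample size: *f* = 0.36, α = 0.05, 80% power, 63 evaluable, 20% dropout, 80 randomised. From Randomisation and allocation concealment: 1:1 allocation. From Statistical analyses and data management: one-tailed tests and exclusion of those without follow-up.

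**1. The plan's own figure.** For a two-group ANOVA, use the noncentral *F* distribution with 1 and *N* − 2 degrees of freedom and λ = *N* × *f*². At two-sided α = 0.05 the smallest *N* with at least 80% power is 63 (80.3%), so the stated 63 is reproduced. For dropout, 63 × 1.2 = 75.6, giving the stated 76; dividing instead gives 63 / 0.8 = 78.75, or 79. The final 80 covers both.

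**2. Loss at the planned dropout.** 0.20 × 80 = 16 without a week-12 score, and 80 − 16 = 64 analysed. Power at 64 is 80.9% two-sided and 88.6% one-sided. Planned attrition therefore costs no planned power.

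**3. Possible bias (assumed values, not in the documents).** Let a fraction *p* of each arm leave, and let *D* be the difference between stayers' and leavers' means in an arm.
- The mean of all randomised is (1 − *p*) × stayers + *p* × leavers, so the completers' mean is off by *p* × *D*.
- With equal dropout, the contrast is off by *p* × (difference in *D* between arms).
- At *p* = 0.20: 0.20 × 0.25 = 0.05 SD and 0.20 × 1.0 = 0.20 SD.
- The planned effect is *d* = 2*f* = 0.72 SD, so the shift is 0.05 / 0.72 = 7% to 0.20 / 0.72 = 28% of it.
- If *D* is the same in both arms, the shift is zero.

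**4. What recovery could do (assumed values).** Suppose a fraction *r* of leavers attend week 12 and are typical of all leavers. Their share of those observed is 0.2*r* / (0.8 + 0.2*r*), against a true share of 0.20.
- *r* = 0.25 (4 of 16): 0.05 / 0.85 = 0.059; the remaining shift is 0.141 × the difference in *D*.
- *r* = 0.50 (8 of 16): 0.10 / 0.90 = 0.111; the remaining shift is 0.089 × the difference in *D*.
- In the 1.0 SD case, the shift falls from 0.20 to about 0.14 or 0.09 SD.

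**5. Capsule counts and guesses.** At endpoint, about 64 of 80 would have them. At midpoint the number lies between 64 (all 16 leave before week 6) and 80 (all leave after); if half leave after midpoint, it is 64 + 8 = 72.

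**The case against.** The strongest objection is that the article condenses a fuller protocol (version 3) that is not shown. Retention steps and early-termination visits are often left to that document, so silence here does not prove that they are absent. This stands. A reader might infer that no week-12 test is ever attempted after early exit; the article neither says so nor rules one out. What it does state is one action for early leavers and an explicit exclusion, and together these leave the outcome missing for anyone handled only as the text describes.

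Second, leaving the study is not the same as stopping capsules. A reader might infer that someone who stops capsules but stays in the study is neither tested nor analysed. The wording does not support that: on its plain reading, such a person who attends week 12 has completed follow-up and is included. The point is only that the article should say so.

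Third, the interview topics are examples and already touch on adherence, so a guess or a reason for leaving could be asked. Those who leave after week 6 have given one count and one guess. A reader might also infer that compliance and blinding will be reported for completers only and will look better than they were. No such report is planned, and the exclusion sentence is argued from the primary outcomes.

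Finally, cost. Endpoint testing is two sessions of 3–4 h on separate days, the Discussion admits a high participant burden in the physiological battery, and recruitment had begun. This limits how many would return but does not weigh against asking for the cognitive session alone.

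**Conclusion.** The point holds in a limited form. As described, early leavers receive a telephone interview, are not said to be invited to week-12 cognitive testing, and are dropped from the analysis. At the planned dropout this affects about 16 of 80 randomised participants.

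The consequence is possible selection bias. Loss of power is a tempting charge, but the figures do not support it: 64 analysed still meets the requirement of 63. The size and direction of any bias cannot be known from the document; 0.05 to 0.20 SD rests on equal 20% dropout in both arms and on assumed between-arm differences of 0.25 to 1.0 SD.

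The gap in capsule counts and guesses is secondary. It is complete only for those who leave before week 6. This is an inexpensive improvement that the sponsor should make, not a fatal flaw.

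**What to change.** 1. In Compliance, success of blinding, safety, and adverse events, state that anyone who stops capsules or leaves early is invited, unless consent is withdrawn, to the week-12 cognitive session with the co-primary tests.
2. In Statistical analyses and data management, state that everyone who attends that session is analysed in the randomised group, whether or not still taking capsules. Without this, the first change may not reach the primary analysis.
3. Use the existing telephone call to record the guess (SLT, placebo or unknown), the date of the last capsule and the reason for leaving. Ask for unused capsules to be sent to the staff member outside the research team who already does the counting.
4. Report compliance and blinding for all who were dispensed medication.

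None of this alters a treatment rule. If the full protocol already provides for these steps, it is enough to say so.

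The cost is a few off-treatment sessions of 3–4 h, a longer call, some postage, and an amendment notified to the ethics committee and the registry. Endpoint visits and travel reimbursement of up to $30 per visit are already planned for every participant. The amendment cannot reach people who have already left.
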